#### Secondary outcome measures

c)Physical Function:
The 30-second Chair Stand test (30 CTS) provides a direct, objective measure (number/times participants can rise to a full standing position from sitting and return to sitting, with arms crossed and held against the chest, in 30 seconds will be counted). The 30 CTS has been recommended within the minimal core set of performance-based outcome measures in OA research and clinical practice [38, 43].The timed up and go (TUG) test evaluates walking speed and mobility and has been found as valid and reliable in KOA patients [43, 44]. Participants are instructed to stand up from a standard height chair and walk at their normal pace around a marker 3 meters away before returning to the chair and sitting down again. TUG has been found as valid and reliable in KOA patients [45].d)PA level:Habitual PA will be measured in three ways, 1) using a questionnaire, 2) second using a scale and 3) using a pedometer.
The Modified Baecke Physical Activity Questionnaire (mBQ), validated in samples adults ≥ 55 years of age [46, 47], to assess PA.The UCLA scale indicates patients’ most appropriate activity level, with 1 defined as “no PA, dependent on others” and 10 defined as “regular participation in impact sports”, and has been found as the only scale discriminating between insufficiently and sufficiently active patients in KOA [48].A pedometer (Yamax SW200 digi-walker) has been compared with actual steps in multiple studies [49–54] and consistently performs well. This pedometer will be clipped to the participants’ waistband on either the left or right hip, each morning and will be removed it at bedtime for 3 consecutive days [54] on three occasions (baseline, week 6 and week 12) to record the number of steps taken per day.e)Health-related QoL: This will be assessed using the Short-Form-12 QoL instrument which is widely used measure of general health and QoL status [55].f)Psychological Function: Tampa Scale for Kinesiophobia (TSK). The TSK will be examined to provide a brief fear of movement scale that is valid and reliable in people with OA [56, 57].

### Sample size

A clinically meaningful difference for the physical function measure of KOOS is considered to be 15%. The margin was derived from a minimal important difference KOOS-pain subscale (MCID_80_ KOOS-PS) score of 10 units reported for the KOOS based on the study by Lyman [58] in KOA patients. It was estimated that individual randomization would require 22 patients in each group participants per arm for a trial with 80% power to detect a 15% difference between trial arms, with a 5% significance level (2-tailed). Fifty-six participants will be recruited to take a 20% drop out rate estimation into account.

#### Randomisation- Allocation concealment

Recruited participants will be randomly allocated to either the experimental group or control group at a 1:1 ratio. Random numbers will be generated using a computer software program run by an external statistician. After baseline assessment, participants will be provided an envelope according to the randomization sequence by a volunteer undergraduate who will prepare consecutively numbered, sealed, opaque envelopes. The envelopes will be kept in a locked location accessible only by the unblinded physiotherapist (MM). The physiotherapist will then schedule the participants’ first appointment.

The investigator (AK) performing all assessments will be blinded to the participant randomization assignment and will not be involved in providing the interventions. Participants will be requested not to disclose details about their treatment to the outcome investigator. The statistician will be blind to group allocation until completion of the statistical analyses.

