### Interventions

During the first face-to-face session (week 1), the physiotherapist (MM) will provide information about KOA and the importance of PA. This introductory session will be scheduled for all participants (both groups) to get familiarized with the webpage environment. Moreover, the journey route of the outdoor walking program, appropriate for each participant will be selected and mutually agreed for both groups. To ensure consistency in content and delivery, the same physiotherapist (with >16 years of postgraduate clinical experience) will take care of the supervision and progression of the program of all participants. Weekly phone supervision to encourage adherence and resolve any issues i.e. potential overload or motivation will be offered to both groups. The weekly dose will be completed for 6 weeks in the community. The participants will be instructed to walk at a moderate level of intensity determined by the Rate of Perceived Exertion Scale (0–10). After completion of the 6-week program (week 7), participants will be encouraged to continue improving PA levels in a second face-to-face session, especially with the walking journey routes, but will not receive any additional intervention till the final follow-up. A final face-to-face appointment will take place in week 12 to support and encourage patients to maintain a PA lifestyle.

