### Strengths and limitations

The study design has several strengths. First, considerable attention has been paid to quality control with the contribution of the established award-winning program ESCAPE-knee pain. Online ESCAPE-knee pain has been found to improve functioning, understanding, and confidence by combining education, advice, and simple coping strategies with functional exercise material [25, 26]. The program does not require specialized training, sophisticated exercises, or equipment for the participants, so it could be implemented and replicated easily. Second, the outcome measures selected are valid, responsive and reliable, cover a range of clinically important concepts, and include those recommended for clinical trials of OA [62]. Third, a well-designed web-based intervention in which patients’ can report their experiences with home exercises via phone calls, provide physiotherapists information about patients’ individual needs for guidance. Research in web-based interventions has focused on interventions without human physical support. Unfortunately, the effects of these interventions have been shown minimal, especially in the long-term [65, 66]. These minimal effects may be partly explained by the absence of face-to-face guidance [67]. Therefore, the combination of web-based intervention with face-to face minimal supervision as well as the inclusion of real life outdoor activity is more promising [65]. The study has been designed with attention to methodological quality characteristics such as randomization, concealed allocation and blinded outcome assessment. Finally, the novelty of the study is that the blended program will be provided in weak structured areas where cost-effective options of physiotherapy care are mostly needed.

Limitation of the study is the unblinded nature of the physiotherapist delivering intervention and guidance. In the case of accessibility limitations during the assessment sessions due to the restrictions imposed by COVID-19 measures will be dealt with telecommunication. Moreover, the level of PA will not be measured objectively prior to the beginning of exercise program.

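### The unblinded treating physiotherapist has sole access to the unopened allocation envelopes, so the concealment claimed as a strength is not secured

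*Protocol article*

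**What the plan says.** All the allocation steps are in the protocol article, section Randomisation- Allocation concealment.

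- **Sequence.** "Random numbers will be generated using a computer software program run by an external statistician". The ratio is 1:1.
- **Preparing and handing out.** After the baseline assessment, "participants will be provided an envelope according to the randomization sequence by a volunteer undergraduate who will prepare consecutively numbered, sealed, opaque envelopes".
- **Storage.** "The envelopes will be kept in a locked location accessible only by the unblinded physiotherapist".
- **Next step.** "The physiotherapist will then schedule" the first appointment.

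Two other sections bear on the point. Under Interventions, one physiotherapist delivers the programme to everyone: "the same physiotherapist (with >16 years of postgraduate clinical experience) will take care of the supervision and progression of the program of all participants". Under Strengths and limitations, the design is credited with "randomization, concealed allocation and blinded outcome assessment". The same section concedes: "Limitation of the study is the unblinded nature of the physiotherapist delivering intervention and guidance". It does not mention that this physiotherapist also holds the envelopes.

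**The concern.** Concealment means that nobody with an interest in who gets which arm can learn or alter the next allocation before the participant is committed to it. Custody of the unopened envelopes is where that protection is kept or lost. Here the stated custodian is the one clinician who treats both arms and knows who is in which.

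The second weakness is that, as written, the person who hands out the envelopes also filled them. Filling envelopes to a sequence ordinarily requires seeing the sequence.

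The trial plans only 56 participants, and its primary measures, KOOS and the pain rating scale, are self-reported. Any steering would fall on a small comparison. The planned ANCOVA adjusts for the baseline value of each outcome. It would not remove steering on traits it does not include, such as motivation or expected adherence.

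**Working it through.** No arithmetic applies, and no sample size, power or significance figure depends on this point. The check sets the statements side by side.

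**1. Who does what**

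| Step | Person named | Where |
|---|---|---|
| Generates the sequence | External statistician | Randomisation section |
| Assesses eligibility | Investigator | Table 1, baseline row |
| Performs all assessments, blinded, does not treat | Investigator | Randomisation section |
| Prepares the envelopes | Volunteer undergraduate | Randomisation section |
| Hands out the envelopes | Volunteer undergraduate, as worded | Randomisation section |
| Has access to the locked store | Unblinded physiotherapist only | Randomisation section |
| Schedules the first appointment | Physiotherapist | Randomisation section |
| Supervises both arms | The same physiotherapist | Interventions |

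**2. Do the hand-out and storage sentences fit together?** Three readings are possible.

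- *The undergraduate dispenses and the physiotherapist unlocks the store and passes on the next envelope.* The sentences are then compatible, but this step is not described. The treating physiotherapist controls every unopened envelope.
- *The undergraduate only prepares, and the hand-out wording is loose.* The dispenser is then unnamed, and the only person who can reach the envelopes is the physiotherapist. The treating clinician is in effect the dispenser.
- *The undergraduate dispenses independently.* The sole-access statement then fails, and the dispenser is the person who prepared the envelopes and so had access to the sequence.

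None of the three separates control of the envelopes from both knowledge of the order and delivery of treatment.

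**3. What the stated safeguards cover**

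- External generation keeps the sequence from being made up locally. It says nothing about custody afterwards.
- Sealing and opacity stop casual reading. They do not stop a custodian with sole, unobserved access from opening and replacing an envelope.
- Consecutive numbering makes reordering detectable only if each number is tied to a participant before opening. No such step is stated.
- Allocation after baseline, with eligibility judged by the investigator, limits selective enrolment. It does not protect the order in which envelopes are used for people already enrolled.
- Blinded assessment protects measurement, not allocation.

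**The case against.** The strongest reply has four parts.

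**The sentences need not conflict.** A reader might infer that the two statements cannot both be true. The document does not support that. The sentences are compressed and can be reconciled by an unstated hand-over, and an article may leave such operational detail to a fuller document. This is accepted, and the point is therefore put as unclear wording. The custody rule is different: it is stated, not omitted, and a fuller hand-over description would not remove it.

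**The route to bias is thin.** Steering by prognosis needs knowledge of the next allocation and of the participant. The physiotherapist is not said to recruit, screen or see baseline data. The first described contact is the week 1 session, and scheduling follows the envelope. The undergraduate has no stated part in eligibility, treatment or assessment, so knowing the order gives that person no stated way to act on it. Nor do the two risks simply add up: sole access by one person limits what the other can do. All of this stands and lowers the risk. It does not make the treating clinician a suitable sole custodian, because concealment should not depend on that person's restraint.

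**The lack of blinding is already disclosed.** It is, but only for delivering the intervention. The same section still claims concealment without mentioning custody.

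**No size can be attached.** A reader might infer that a few steered participants would shift the KOOS difference by a material part of the 10-unit margin in the sample size section. Any such figure needs an assumed number of steered participants and an assumed difference in prognosis, and the document gives neither. The ANCOVA on baseline would also remove part of any shift, by an amount that cannot be determined. This objection stands in full, and no magnitude is claimed.

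**Conclusion.** The point holds as a weakness in the stated procedure. The unblinded physiotherapist who treats both arms has sole access to the unopened envelopes. The person who hands them out, as worded, also prepared them, and how the two arrangements work together is unclear. The existing safeguards reduce the exposure but leave opening, swapping and reordering by the custodian possible. The claim of concealed allocation is therefore not secured.

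This is a risk, not evidence that any allocation was or would be steered, and its size cannot be derived. The conclusion rests on two assumptions: that the storage sentence means what it says, and that preparing the envelopes gave the undergraduate sight of the sequence. The second is an inference from the task and is not stated. The custody point does not depend on it.

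**What to change.** 1. Remove the physiotherapist's access to unopened envelopes.
2. Give custody and release to one named existing role with no part in recruitment, treatment, outcome assessment or the blinded analysis. The external statistician is suitable only if that is not the statistician who, under the same section, must stay blind until the analyses are finished. The document does not say whether these are two people, and releasing allocations one by one would break that blinding if they are the same.
3. Separate preparing from dispensing: whoever fills the envelopes does not hand them out.
4. Once eligibility and baseline data are logged, write the participant's identifier on the next numbered envelope before it is opened, and keep a record.
5. Tell the physiotherapist the arm only when the first session is to be scheduled.
6. Rewrite the hand-out and storage sentences so that they describe one procedure.

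If allocation has already taken place, report the procedure actually used and qualify the concealment claim under Strengths and limitations.

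The cost is small: a reassignment of tasks, a short log and an edit to the text. It needs no extra participants or change to the analysis. It needs no new staff provided an existing person meets the independence conditions, which the sponsor must confirm.

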#### Statistical analysis

We will calculate the proportion of enrolled participants out of all eligible patients, the adherence rate and the dropout rates. The Shapiro-Wilk Test will be used to determine the normality of the data. Descriptive statistics will be presented for each group as mean change (standard deviation (SD), 95% confidence intervals) for all outcomes from baseline to 12 weeks. Analysis of covariance (ANCOVA) will be performed using IBM SPSS version 24 for all the primary and secondary outcome measures with baseline measures as covariates. In the case of missing data in the relevant directions according on how to handle missing data in every outcome measure will be followed.

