#### Adherence strategies

To increase the likelihood of adherence to the interventions, the following behavioural change techniques and strategies will be used. First, each participant will have a planning session with a physiotherapist of up to 30 min to plan the location, day and time of day for each walk, and reinforce that each walk was moderate intensity in at least a 10 min. Second, regular physiotherapy supervision and monitoring each week with regular phone calls based on patient preference will be offered. If any complication or query should arise, participants could discuss it in the weekly phone calls or contact directly the physiotherapist, and they will be informed of the procedure to follow. Third, each participant will wear a pedometer and record the number of steps taken and time spent walking during each session in a logbook. All participants will complete the daily logbook to record the time (in minutes) spent in activity either walking or exercising in for each walking session over the 12 weeks (Table 2). The physiotherapist will monitor the participant’s logbook at each weekly supervisory session (by phone). Fourth, participants will be encouraged to engage social supports such as walking with a friend, family member if they chose to. They will also describe any changes to their usual care of their KOA and any problems with their knee while doing their walking program each week.

**Table 2 pone.0268652.t002:** Logbook diary to monitor compliance, duration and frequency of exercise and outdoor walking activity weekly.

	Week 1		Week 2		Week 3		Week 4…	..Week 10	Week 11	Week 12
	Exercise (-/min)	Walking (-/min/step)	Exercise (-/min)	Walking (-/min/steps)	Exercise (-/min)	Walking (-/min/steps)	Exercise (-/min)	…	…	Walking (-/min/steps)
Monday										
Tuesday										
Wednesday										
Thursday										
Friday										
Saturday										
Sunday										

Participants in both groups will be free to withdraw from the study at any time, but the withdrawal rates and reasons will be recorded.

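### The only missing-data rule, following each instrument's directions, cannot supply a score for a missed assessment, so the ANCOVA omits anyone without a score at that visit despite 20% expected dropout

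*Protocol article*

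**What the plan says.** The Statistical analysis section fixes two things. The model is given as "Analysis of covariance (ANCOVA) will be performed using IBM SPSS version 24 for all the primary and secondary outcome measures with baseline measures as covariates". For missing data, "relevant directions according on how to handle missing data in every outcome measure will be followed". The same section reports dropout rates as a descriptive figure.

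Under Sample size, "individual randomization would require 22 patients in each group", and "Fifty-six participants will be recruited to take a 20% drop out rate estimation into account". Under Adherence strategies, "Participants in both groups will be free to withdraw from the study at any time", with withdrawal rates and reasons to be recorded. Assessments are at baseline, week 6 and week 12. The Introduction makes week 6 the main comparison and maintenance at week 12 the secondary one.

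The article does not name an analysis set, a method for missed assessments or a sensitivity analysis.

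**The concern.** An instrument's directions deal with gaps inside a completed form. The plan expects a different kind of gap, in which the participant is not assessed at all. No scoring manual covers that. Several outcomes are also single values: the NPRS (listed as primary), TUG, the 30-second chair stand, the UCLA scale and the pedometer count.

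An ANCOVA of a follow-up score on group and baseline uses only participants who have that score. At week 12 it also ignores what week 6 showed about those who have since left. If loss is related to outcome and differs by arm, the participants left for comparison are no longer the groups that were randomised. Recruiting extra participants protects power among those who remain; it does not protect against this bias. Loss after week 6 is plausible, because no further intervention is given between the week-7 session and the final follow-up.

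**Working it through.** **1. The plan's own figure.** 22 / (1 − 0.20) = 27.5, rounded up to 28 per arm, 56 in total. This reproduces. Expected loss is 0.20 × 56 = 11.2, so about 11 participants could have no score at a visit, and the stated rule gives no value for them.

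**2. Inputs the documents do not give.** No SD, between-visit correlation, dropout timing or dropout mechanism is stated. Solving the two-means formula backwards (two-sided 5%, 80% power, 22 per arm) gives a standardised difference of (1.960 + 0.842) × √(2/22) = 0.845. That implies an SD of 10/0.845 = 11.8 if the target is 10 units, or 15/0.845 = 17.8 if it is 15 units. The illustration assumes SD 17 and correlations of 0.5 (baseline with week 6), 0.5 (baseline with week 12) and 0.7 (week 6 with week 12).

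**3. Hand calculation for week 12, no true effect.** Assume that in the experimental arm those below the mean at week 6 are lost with probability 0.48 and the rest with 0.10, an overall loss of (0.48 + 0.10)/2 = 29%. In the control arm 10% are lost at random. The mean of a standard normal above zero is √(2/π) = 0.798.

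- Week-6 mean among experimental-arm completers: 0.798 × (0.5 × 0.90 − 0.5 × 0.52) / 0.71 = 0.214 SD.
- Their baseline mean: 0.5 × 0.214 = 0.107 SD. Their week-12 mean: 0.7 × 0.214 = 0.149 SD.
- ANCOVA difference, with a baseline slope of about 0.5: 0.149 − 0.5 × 0.107 = 0.096 SD, or 0.096 × 17 ≈ 1.6 points.

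Simulation of 4,000 trials with this pattern gave +1.7.

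**4. Range over dropout patterns** (28 per arm, no true effect, loss after week 6):

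| Loss, experimental v control | Mechanism | Week-12 bias of ANCOVA |
|---|---|---|
| 20% v 20% | same outcome-related mechanism in both arms | 0.0 |
| 25% v 15% | milder selection | +0.9 |
| 29% v 10% | the two-level rule of step 3 | +1.7 |
| 29% v 10% | logistic on week-6 score, slope 1, 1.5 or 2 per SD | +1.8, +2.5, +2.8 |

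Bias scales with the SD. At SD 11.8 the last row becomes 1.8 × 11.8/17 = 1.2 to 2.8 × 11.8/17 = 1.9. The positive sign follows from assuming that poor responders leave the experimental arm; the opposite pattern would reverse it.

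**5. Using the week-6 scores.** A likelihood estimate takes the group coefficient from regressing week 12 on group, baseline and week 6. It then adds the week-6 coefficient times the group effect on week 6 among all those seen at week 6. Over these settings its bias stayed within about 0.15 points. The SD of the estimate was 4.3 to 4.4, against 4.4 to 4.5 for ANCOVA, so precision is not lost.

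**6. Loss before week 6.** Apply the step 3 loss pattern to a week-6 score that is never observed. The week-6 ANCOVA bias is (0.214 − 0.5 × 0.107) × 17 ≈ 2.7 points, as simulation also gave. A repeated-measures model has no follow-up from these participants either, so the bias is unchanged.

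**The case against.** The strongest reply is that this is a condensed article, and that analysis sets and missed-visit methods usually sit in a fuller plan. That plan is not shown and may add a rule. But the article is not silent: it states a rule and a model, and together they do not cover the dropout that the article itself predicts.

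Other limits do stand:

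- A reader might infer that the plan adopts a completers-only analysis, or that every dropout is lost to it. The documents do not say so. Someone who leaves after week 6 still counts at week 6, and someone who stops the programme but attends assessment counts at both visits. Remote assessment under COVID-19 restrictions and the weekly calls may prevent some missed visits. Fitting ANCOVA separately at each visit is itself a reading of a brief text.
- A reader might infer a bias of two points or more in favour of the experimental arm. That is an adverse scenario, not a prediction; the range starts at zero. Unequal burden is also uncertain, since the control arm walks five times a week expressly to equalise dosage.
- A reader might infer that a mixed model cures the problem. It helps mainly at week 12, and its near-zero bias here depends on dropout being explained by observed week-6 scores.
- Baseline-adjusted ANCOVA is a valid analysis, the precision gain from the alternative is small, and multiple imputation would serve equally well.

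**Conclusion.** The point holds in a limited form. As stated, the rule handles item gaps but not missed assessments. With ANCOVA as the only model, a participant without a score at a visit leaves that visit's analysis, and earlier follow-up is not used at week 12.

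The size and direction of any bias cannot be known from the documents. Under the assumed SD of 17 and correlations, week-12 bias lies between 0 and about 2 to 3 points, up to about a quarter of the 10-unit difference cited under Sample size. It is smaller if the SD is smaller. The inflation from 22 to 28 per arm is correct and is not in question.

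This should be corrected before analysis because the remedy is cheap, but it does not invalidate the design.

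**What to change.** In the Statistical analysis section:

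1. Restrict the instrument directions to unanswered items in a returned form.
2. State that all randomised participants are analysed in the arm to which they were allocated.
3. Use one baseline-adjusted likelihood model for repeated measures over weeks 6 and 12 (group, visit, group-by-visit, baseline, baseline-by-visit, unstructured covariance), or equivalent multiple imputation. Report the week-6 and week-12 contrasts from it.
4. Add a delta-adjusted sensitivity analysis covering every randomised participant, including those with no follow-up, because the main model adds no information about anyone lost before week 6.

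The cost is new wording and slightly more analysis work, and the planned SPSS package can fit the model. The sample size of 56 and all patient procedures stay as they are.
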